### 3.2 Sample size

20 subjects in each group

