### 3.3 Study design

Randomization: using a computer-generated randomization sequence

Group assignment:

- Group A: acupuncture at active acupoints
- Group B: acupuncture at inactive acupoints
- Group C:acupuncture at acupoints on other meridians

Patients will be blinded to group assignment. Data management and analysis will be performed by researchers who are blinded to the acupuncture procedures.

Study schedule:

The total observation period within this study is 12 weeks for each patient. All patients will be asked to document their headache diaries, and the outcome measurement is completed both in the baseline and 4 and 8 weeks after randomization. Resting-state fMRI scans will be performed on each group before and after treatment to detect the local features of spontaneous brain activity.

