### 3.4 Treatment schedule

3.4.1 Group assignment and acupoint selection

- Group A:SJ5 (Waiguan), GB20 (Fengchi), GB34 (Yanglingquan), GB40 (Qiuxu)
- Group B: SJ22 (Erheliao), PC7 (Daling), GB37 (Guangming), SP3 (Taibai)
- Group C: PC3 (Quze), PC6 (Neiguan), LR3 (Taichong), LR5 (Ligou)

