3.4.2 SOP of manipulation

Traditional Chinese style acupuncture will be used and treatments are manipulated by specialized acupuncturists with at least five years’ training and three years’ experience.

The acupoints of all groups are asked to achieve *DeQi* sensation by lifting and thrusting combined with twirling and rotating the needles. All the groups are asked to retain the needles for 30 minutes, and close the acupoint holes with clean cotton balls to avoid bleeding when withdrawing the needle.

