### 3.8 Statistical analysis

Clinical data analysis: Baseline data, demographic data and scale data will be analyzed by the SPSS 14.0 statistical software (SPSS Inc., Chicago, IL, USA). All analyses were based on the PP population. Chi-square test will be used to examine differences between groups (95% CI, 2-sided). The general linear model repeated measures procedure was used to test the differences in the repeated continuous variables (*Deqi* sensations) between the two groups.

Functional MRI image analysis: After data preprocessing conducted on SPM5 software, regional homogeneity and functional connectivity analysis will be performed to detect the modulation of different acupuncture interventions on pain-related functional networks at two time-points (prior to acupuncture, and after acupuncture treatment).

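### The repeated-measures test of Deqi sensations is written for two groups, although three are randomised and Deqi is collected in all of them

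*Protocol*

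**What the plan says.** Section 3.3 of the protocol lists three randomised arms: "Group A: acupuncture at active acupoints", "Group B: acupuncture at inactive acupoints" and "Group C:acupuncture at acupoints on other meridians". Section 3.4.1 gives each arm its own set of four points. Section 3.2 plans "20 subjects in each group". The purpose statement at the start sets all three kinds of acupoint against one another.

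Section 3.4.2 aims for the Deqi sensation in every arm: "The acupoints of all groups are asked to achieve" it. Section 3.6.2, item (4), has the sensation recorded after needle removal at the 8th, 16th, 24th and 32nd sessions and makes no distinction by arm.

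Section 3.8 then says that a repeated-measures general linear model "was used to test the differences in the repeated continuous variables", names Deqi sensations as those variables, and ends with "between the two groups".

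**The concern.** The number of groups in the analysis sentence does not match the number in the design. This is not detail that a protocol may leave to the SAP. The protocol has fixed the number of groups compared, and fixed it in conflict with its own design. An SAP that followed section 3.8 to the letter would contradict sections 3.3 and 3.4.1.

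What is at stake is the Deqi comparison. The trial asks whether brain responses differ by type of acupoint. If needling sensation also differed between arms, a difference in brain response could reflect sensation rather than choice of point. The protocol does not state that Deqi is measured for this reason, but it is the natural use of the data, and it needs every arm that enters the brain comparison. A two-group model leaves one arm unchecked and does not say which.

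**Working it through.** No figure in the plan can be reproduced here. Section 3.2 gives 20 per group without effect size, SD, power or alpha. The check is a count, set against the text.

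**Count of groups**

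| Place in protocol | Groups |
| --- | --- |
| Purpose | 3 |
| 3.3 Study design | 3 (A, B, C) |
| 3.4.1 Acupoint selection | 3 |
| 3.4.2 Deqi sought | all |
| 3.6.2 (4) Deqi recorded | no restriction by arm |
| 3.8 Deqi model | 2, not identified |

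Three pairs fit the wording of section 3.8: A-B, A-C and B-C. They are not interchangeable, since the arms are defined by different kinds of acupoint. Pooling two arms against the third would also make two groups, but no pooling is described.

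**What a literal two-arm model leaves out**, taking 20 evaluable patients per arm:

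- Patients: 3 × 20 = 60 planned and 2 × 20 = 40 in the model, so 20 of 60 (one third) are omitted.
- Deqi records: 60 × 4 sessions = 240 planned and 40 × 4 = 160 used, so 80 are omitted.
- Group factor: 3 − 1 = 2 df with all arms, against 2 − 1 = 1 df.
- Between-subject residual: 60 − 3 = 57 df, against 40 − 2 = 38 df.
- Group-by-session interaction: (3 − 1)(4 − 1) = 6 df, against (2 − 1)(4 − 1) = 3 df.

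**Which model terms are needed.** Section 3.6.2 lists no Deqi value before treatment; the first is at session 8. The interaction therefore shows only whether the arms diverge between sessions 8 and 32. A difference present from the first recording and constant afterwards appears only in the group main effect. Both terms have to be reported.

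**Illustration of why pairwise comparisons need adjustment.** This assumes two-sided alpha 0.05; section 3.8 gives a two-sided 95% interval only for the chi-square test. For one outcome at one time point:

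- Three unadjusted tests: 1 − 0.95³ = 0.143 if independent; about 0.124 when simulated with shared arms and 20 per arm (100,000 runs).
- Two unadjusted tests: 1 − 0.95² = 0.0975 if independent; about 0.093 simulated.

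**Cost of adjusting.** The detectable standardised difference at an assumed 80% power is (z for 1 − α/2 + z for 0.80) × √(2/20):

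- α = 0.05: (1.960 + 0.842) × 0.316 = 0.89 SD
- α = 0.025: (2.241 + 0.842) × 0.316 = 0.97 SD
- α = 0.05/3 = 0.0167: (2.394 + 0.842) × 0.316 = 1.02 SD

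**The case against.** The strongest reply is that this is a slip of one word on a minor measure. Deqi is sought and recorded in all groups, so all three would probably be analysed whatever the sentence says, and nothing shows an intention to choose a pair after seeing the data. This may be so, and the wording may have come from a two-arm text, though the document cannot confirm that. The reply lowers the weight of the point but does not remove it: the sentence is the protocol's stated rule for this analysis, and it is wrong as written.

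The reply is fully right about scope. A reader might infer any of the following, and the protocol supports none of them:

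- **An arm is dropped from the main comparisons.** The sentence covers Deqi only. The chi-square sentence speaks of groups without a number, and the fMRI sentence refers to the different interventions. Neither is limited to two arms.
- **The plan has a false-positive rate of about 12%.** That figure belongs to three unadjusted pairwise tests at a single time point. The protocol proposes a repeated-measures model, not such tests.
- **A-B and A-C should rank above B-C because Group B's points share meridians with both other arms.** The codes do overlap: "Group B: SJ22 (Erheliao), PC7 (Daling), GB37 (Guangming), SP3 (Taibai") includes SJ and GB points, as Group A does, and a PC point, as Group C does. But B is defined as the inactive-point arm, so the overlap contradicts nothing, and the purpose names the three arms without ranking contrasts.

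**Conclusion.** The contradiction is real, and nothing in the protocol resolves it. Three groups are randomised and have Deqi recorded, but the stated Deqi model compares two that are not named. Taken literally, it omits 20 of 60 planned patients and 80 of 240 Deqi records, and the stated test then cannot address comparability of needling sensation across all three arms. These counts assume that every planned patient is evaluable. Section 3.8 restricts analysis to the per-protocol population, so actual numbers may be smaller.

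The consequence stops at the Deqi analysis. The fMRI and headache analyses are not affected by this wording. The family-wise error figures are illustrative and do not measure an error in the plan. The sentence is a wrong analysis rule and should be corrected, but on a process measure it is a moderate point and not one on which the trial's main conclusions depend.

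**What to change.** In section 3.8, replace the closing words of the Deqi sentence with: *among the three groups (A, B and C), with group as a three-level between-subject factor and session (8, 16, 24, 32) as the within-subject factor, reporting the group main effect and the group-by-session interaction; any pairwise group comparisons are adjusted for multiplicity (for example by Holm's method)*.

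No ranking of the pairwise contrasts is needed.

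The change is to wording only: no new data, visits or patients. The downside is a stricter threshold for pairwise comparisons. With Holm over three pairs, the smallest p-value must be below 0.0167, which at an assumed 80% power and 20 per arm raises the detectable difference for that comparison from 0.89 to 1.02 SD. The overall group and interaction tests carry no such penalty. If the sponsor does intend a two-group comparison, the protocol should name the pair and give the reason for leaving out the third arm.
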